## Abstract

**Background:**

Fatty liver disease is characterized by the accumulation of fat vacuoles inside of the hepatocytes. Non alcoholic fatty liver is associated with obesity, type 2 diabetes, dyslipemia, the intake of certain drugs and with the so-called metabolic syndrome. However, there is little information on the clinical relevance of this disorder as a healthcare problem in the general population, since the studies published generally include a limited number of patients and the diagnosis is established on the basis of clear biochemical alterations and liver biopsy.

**Methods/Design:**

The aim of the study is the prevalence of non-alcoholic fatty liver disease in a general adult population by hepatic ultrasonography.

A population-based, descriptive, transversal, multicentre study. Eighteen primary care centres of the north of Barcelona and the Maresme Areas of Healthcare Management attending an urban and semi-urban population of 360.000 inhabitants.

A randomized sample of 786 subjects of 15 years or older were selected from the population and assigned to the participating centres according to the Primary Care Information System (SIAP): This population is practically the same as the general population of the area.

The following determinations will be carried out in all the participants: hepatic ultrasonography to detect fatty liver, a questionnaire concerning liver diseases, alcohol intake, smoking and drug use, physical examination including abdominal perimeter and body mass index and biochemical analysis including liver function tests and parameters related to the metabolic syndrome and the HAIR score.

Ultrasonographic diagnosis of fatty liver will be made according to established criteria (American Gastroenterology Association) and diagnosis of metabolic syndrome according to the criteria of the European Group for the Study of Insulin Resistance.

**Discussion:**

This study will attempt to determine the prevalence of non alcoholic fatty liver disease, as well as, the factors most frequently associated with the presence of this disease to thereby achieve the most appropriate treatment and avoid the evolution of the disease.

## Background

Fatty liver disease is characterized by the accumulation of fat vacuoles in the cytoplasm of the hepatocytes, and is usually a mild lesion which is generally detected in chronic alcoholic patients [1].

Until the appearance of hepatic ultrasonography, fatty liver was a disorder diagnosed only by liver biopsy in individuals presenting hepatomegaly with or without biochemical abnormalities suggestive of liver disease [1,2].

At the beginning of the 1980s, a liver lesion was described which could not be differentiated from that associated with alcohol, and which covered a wide spectrum of patterns including simple fatty liver, steatohepatitis, with fatty vacuoles, necroinflammatory changes and a variable grade of fibrosis which may finally progress to liver cirrhosis in subjects without significant alcohol consumption [3,4]. Non alcoholic fatty liver is associated with factors such as obesity, type 2 diabetes, dyslipemia, the intake of certain drugs (amiodarone, oestrogens, and corticoids) and with the so-called metabolic syndrome (obesity, type 2 diabetes, dyslipemia, and arterial hypertension) [5-9].

Few studies have evaluated the prevalence of fatty liver in a general population. Along this line, the widest study undertaken was performed in a sample of almost 7.000 subjects in Northern Italy. In this study the most prevalent hepatic lesion was fatty liver (33% of the subjects with excessive alcohol intake) but ultrasonographic diagnosis was only performed in cases presenting clinical or analytical alterations suggestive of liver disease [10,11]. The same authors have recently published the results of another study with a new review of the prevalence and risk factors associated with fatty liver in the same series of patients and concluded that fatty liver is very prevalent (20%) in the general population and is associated with the different components of the metabolic syndrome [12]. Thus, non alcoholic fatty liver may be the hepatic component of the metabolic syndrome. Another study published in Spain attempted to make an epidemiologic approach to fatty liver by prospectively determining the prevalence, diagnosed by abdominal ultrasonography of 1703 working males and studying the relationship with alcohol intake and other risk factors such as obesity (body mass index > 30), hypercholesterolemia and hyperglycaemia and found that 13.8% fulfilled ultrasonographic criteria of fatty infiltration. Logistic regression analysis identified alcohol consumption > 40 g/day, age, obesity and elevated values of glycaemia, cholesterol and gammaglutamyltransferase as the main factors associated with the presence of fatty liver in this population [13].

More recently a population study has been published including 420 patients diagnosed with fatty liver not related to alcohol from 1980 to 2000 in different primary, secondary and tertiary healthcare centres in Minnesota. The authors precisely defined the morbidity and mortality associated with this disease. The patients had a mean age of 49 years, two out of three were obese and had hypertriglyceridemia, 36% were hypertensive, 26% had diabetes and 36% presented altered baseline glycaemia. The mean follow up of the patients was of 8 years. During this time period 13% of the patients died, representing a mortality greater than that expected in the general population (RR 1.34; p = 0.03). On multivariate analysis, the predictive factors of mortality were age, the presence of cirrhosis and surprisingly, altered baseline glycaemia. Liver disease constituted the third cause of death in these patients following neoplasms and ischaemic heart disease, in contrast with the general population in whom liver diseases are the thirteenth cause of death. Specifically speaking, during the follow up period, 5% of the patients were diagnosed with cirrhosis, 3% presented complications and 7 patients died in relation to their chronic liver disease (1.7%) [14].

The pathogenesis of non alcoholic fatty liver is only partially known, although it seems to be multifactorial. The most widespread pathogenic theory is that of the double impact in which the first is a resistance to peripheral insulin resulting in the accumulation of fat in the liver, and the second is chronic oxidative stress which leads to apoptosis and/or hepatocellular necrosis, inflammation and fibrosis [15,16].

As we have seen, the main risk factor for the development of non alcoholic fatty liver is, therefore, obesity. It is well known that the increase in the number of obese persons within the general population has progressed up to the point that the healthcare authorities consider it to be one of the main healthcare problems for the near future and making it one of the priorities for intervention and investigation. In addition, patients with non alcoholic fatty liver who are overweight and/or obese are more to likely to develop non alcoholic steatohepatitis, with a percentage of these patients evolving to more severe forms of liver disease. We therefore believe that it is important to determine the HAIR score established by Dixon et al [17] to know which patients may evolve to more severe forms of the disease. The HAIR score includes: arterial hypertension, insulin resistance defined as: type 2 diabetes with baseline glycaemia values greater than 110 mg/dl and less than 126 mg/dl and two of the following factors: arterial hypertension, triglycerides above 150 mg/dl and/or HDLc < 35 in males and < 39 in females, a waist/hip index > 0.90 in males and 0.85 in females and/or BMI > 30 Kg/m2, and ALT levels >40. Patients with a HAIR score ≥ 2 are considered to have a high probability of developing non alcoholic steatohepatitis.

The metabolic syndrome is constituted by the presence of a series of factors within the same subject such as obesity, arterial hypertension, dyslipemia or glucose intolerance and has been on the rise in recent years. Several criteria are used to define the metabolic syndrome, with the most commonly used being those of the World Health Organization (WHO) [18] and those of the Adult Treatment Panel III (ATP-III) of the National Cholesterol Education Program (NCEP) [19]. The criteria of the WHO require the presentation of some alteration in carbohydrate metabolism, whether diabetes, abnormal glucose tolerance or resistance to insulin. Two of the following criteria must also be taken into account: arterial hypertension > 140/90 mm Hg, obesity (BMI = 30 Kg/m^2^), hypertriglyceridemia ≥ 150 mg/dL or cHDL values < 35 in males and < 40 in females and microalbuminuria ≥ 20 μg/min. This definition places great importance on alterations in carbohydrate metabolism and insulin resistance as the elements necessary for the diagnosis of the metabolic syndrome. However, the definition by the WHO requires the presence of an alteration in glycaemia and does not place importance on the presence on abdominal obesity which is important to define insulin resistance. For this reason the European Group for the Study of Insulin Resistance (EGIR) has proposed several changes in the definition of the WHO, such as the presence of obesity (waist perimeter ≥ 94 cm), fasting plasma insulin determination and altered fasting glycaemia [20]. The criteria of ATP-III of the NCEP are based on the presence of abdominal obesity (≥ 88 cm in women and ≥ 102 cm in males), hypertriglyceridemia (≥ 150 mg/dL), low cHDL plasma values (<35 mh/dL), arterial hypertension (≥ 130/85 mm Hg) and altered fasting glycaemia (≥ 110 mg/dL). The criteria of the ATP-III are more clinical and easier to apply than those of the WHO, but the results of several studies have shown that the ATP-III criteria overestimate the presence of the metabolic syndrome. On the other hand, the criteria of the ATP-III do not correlate with those using insulin resistance as the fundamental element of diagnosis. Given the importance of the metabolic syndrome in the diagnosis of non alcoholic fatty liver and the discrepancies between the two models, we believe it may be useful to analyze both models in all the subjects to determine wihch model best defines the metabolic syndrome.

### Objectives

#### Main objectives

1. Determine the prevalence of non alcoholic fatty liver in apparently healthy adults who do not request medical care and who have undergone a hepatic ultrasongraphy.

2. Describe the associated characteristics of these subjects based on: sociodemographic variables, history of liver disease and associated risk factors.

3. Evaluate the influence of each of the components making up the metabolic syndrome and the risk of having non alcoholic fatty liver.

4. Identify the subjects who may progress to chronicity and the factors favouring progresión.

#### Secondary objectives

1. Identify a cohort of patients with fatty liver with no evidence of previous liver disease to perform a prospective follow up.

## Methods/Design

We will carry out a descriptive, transversal, population-based, multicentre study in apparently healthy adults (older than or equal to 15 years of age) or subjects not requesting medical care who have undergone a hepatic ultrasonography. The study has been approved by the Ethical Committee of Clinical Investigation, Jordi Gol i Gurina Foundation.

### Study subjects

This will be a multicentre study including the participation of Primary Care teams covering a population of 360,000 inhabitants of an urban, and semi-rural zone of the North of Barcelona and the Maresme, Spain.

#### Inclusion criteria

Adult population of both sexes from these Primary Care teams between the age of 15 and 80 who wish to voluntarily participate in the study and who have signed a written informed consent form to participate.

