### Sample size

With an alpha risk of 0.05 for a precision of ± 0.03 percentage units in a bilateral contrast for an estimated proportion of 0.20 a randomized sample proportional to 683 subjects is required. Considering that 15% of the population will present alcohol intake or some previous liver disease, the number of patients to study in this percentage is increased making a total of 786 individuals necessary to fulfil the final sample size.

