### Selection method

A randomized sample of the population assigned and obtained through the SIAP (Primary Care Information System), will be stratified in proportion to the population assigned to each of the Primary Care teams participating in the study. It should be pointed out that the population assigned is practically equivalent to the updated municipal pattern.

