### Plan of analysis

Data will be introduced into an ACCESS type database and then analysed. The prevalence of fatty liver will be estimated with a confidence interval of 95%.

A descriptive univariate and bivariate statistical analysis will be performed, analysing the qualitative variables with chi-squared test and the quantitative variables with the Students-t- test. Statistical significance will be established at 5% for all the bivariate analyses and contrasts will be considered at a bilateral level. Multivariate analysis will also be undertaken with logistic regression models (dependent variable presence/absence of fatty liver) allowing adjustment of the effect of the different independent variables on the presence of non alcoholic fatty liver.

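### The figure of 786 is given both as the number drawn from the register and as the number needed, with no allowance for refusals, people over 80 or other exclusions

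*Protocol article*

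**What the plan says.** The abstract (Methods/Design) states: "A randomized sample of 786 subjects of 15 years or older were selected from the population". The opening of the main Methods/Design section also gives 15 years and over, with no upper limit. The Inclusion criteria narrow this to people "between the age of 15 and 80 who wish to voluntarily participate in the study" and require signed consent. The Exclusion criteria remove those above the alcohol limits, those with chronic liver disease or positive hepatitis B or C markers, and those who are incapacitated, cognitively impaired, institutionalised, without a fixed address in the area, or who do not consent.

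The Sample size section works from "With an alpha risk of 0.05 for a precision of ± 0.03 percentage units in a bilateral contrast" and continues "for an estimated proportion of 0.20 a randomized sample proportional to 683 subjects is required". It then adds 15% for alcohol intake or earlier liver disease and arrives at 786 as the total required.

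Under Selection method, the random sample from the primary care information system (SIAP) "will be stratified in proportion to the population assigned to each of the Primary Care teams participating in the study". The Plan of analysis says "The prevalence of fatty liver will be estimated with a confidence interval of 95" per cent. It does not say whether the estimate is weighted or unadjusted.

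**The concern.** One number fills two roles that match only if everyone drawn is eligible, apart from the alcohol and liver exclusions, and agrees to take part. The article's own criteria rule that out: they describe refusers, an age group inside the stated draw but outside the eligible range, and further exclusions that the 15% was not meant to cover. The article states its inflation and the reason for it, so the mismatch lies in what it says and not in a detail it left out.

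Two things are at stake. The first is the planned precision of the primary estimate. The second is the population to which it refers. The study aims at prevalence in the general population, and proportional allocation protects that only by care team and only before non-response. The Background lists age among the factors associated with fatty liver in one study of working men. If participation differs by age, the estimate could shift in a way that its confidence interval would not show.

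**Working it through.** **Inputs from the article.** Expected prevalence 0.20; half-width 0.03, read as 3 percentage points; two-sided alpha 0.05; 683 evaluable; 15% allowance; total 786; draw aged 15 or older; eligibility 15 to 80.

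**Inputs assumed.** The article gives no response rate and no share of people over 80. I use 60% to 100% for response and 3% to 8% for the share over 80.

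**Step 1: the plan's own figures.** n = z² × p(1 − p) / d² = 1.96² × 0.20 × 0.80 / 0.03² ≈ 682.9, rounded up to 683. Then 683 × 1.15 = 785.45, rounded up to 786. Both figures reproduce. (Dividing by 0.85 instead of multiplying by 1.15 gives 803.5, that is 804. The difference of 18 is small and is not the point here.)

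**Step 2: yield if 786 is the number drawn.** Evaluable m = 786 × 0.85 × r, where r is the response. Half-width = 1.96 × √(0.16 / m). The draw needed for 683 evaluable is 683 / (0.85 × r).

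| Response r (assumed below 100%) | Evaluable m | Half-width (points) | Draw needed |
|---|---|---|---|
| 100% | 668 | ±3.03 | 804 |
| 90% | 601 | ±3.20 | 893 |
| 80% | 534 | ±3.39 | 1005 |
| 70% | 468 | ±3.63 | 1148 |
| 60% | 401 | ±3.92 | 1340 |

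**Step 3: people over 80 alone, with full response.** At 3% of the draw, 786 × 0.85 × 0.97 = 648 remain (±3.08). At 8%, 786 × 0.85 × 0.92 = 615 remain (±3.16). This adds about 0.05 to 0.13 point to the ±3.03. The other exclusions cannot be sized from the article.

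**Step 4: scale of a possible shift in the estimate.** Bias = (1 − r) × (prevalence in participants − prevalence in refusers). With r = 0.70 and an assumed difference of 5 to 10 points, this is 0.30 × 5 = 1.5 to 0.30 × 10 = 3.0 points. The upper end equals the whole planned half-width. The difference is an assumption chosen to show scale; nothing in the article estimates it.

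**The case against.** The strongest reply is that the article never says 786 is the number invited. The Sample size section presents the increase as one in the number of people to be studied. Alcohol intake and the hepatitis markers, which the 15% partly covers, are established during the study's own assessment. An allowance for exclusions found at examination fits a count of consenting people who attend. On that reading 786 × 0.85 = 668 and ±3.03 points, which is essentially on target. The abstract's wording about selection is compressed and may mean no more than this. The reply stands as far as it goes: the text is ambiguous, and the shortfall is conditional on one reading.

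A reader might also infer that the analysis will use a crude proportion and that precision and representativeness therefore fail. The article does not support this. The Plan of analysis is silent on weighting, which a condensed article may leave to a fuller document. Proportional allocation is self-weighting by team before non-response. No response rate is given, and selective participation is a risk that the article neither shows nor rules out. Nor does it state the direction or size of the age association.

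Fine weighting would also be unsound. With 18 centres, 2 sexes and, say, 4 age bands there are 144 cells, and 683 / 144 is fewer than 5 subjects per cell. Weighting cannot correct selection within a cell. The register's age-sex structure also includes people whom the criteria exclude.

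The reply does not remove the double use of 786, the conflicting age limits, or the absence of any stated allowance or replacement rule for losses that the article itself describes.

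**Conclusion.** The point holds in a limited form. The article uses 786 both as the number drawn and as the number needed, inflates it only for alcohol intake and liver disease, and gives age limits that disagree. If 786 is the draw, the ±3 points is not protected. The half-width is about ±3.2 to ±3.9 points at an assumed 90% to 60% response, and people over 80 make only a small further difference. If 786 is the number examined, precision is practically as planned and what remains is a matter of wording and of the age range. The loss of precision is moderate on either reading. A shift in the estimate from selective participation is possible but cannot be sized from the article. Standardisation is therefore a worthwhile safeguard and does not correct a stated error.

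**What to change.** 1. Reconcile the age range across the abstract, the Methods/Design opening and the Inclusion criteria, and limit the SIAP draw to ages 15 to 80.
2. State that the target is the number of people examined, with further random draws in the same team strata until it is reached. Alternatively, keep the draw at 786 and restate the precision for the expected yield, giving the assumed response.
3. Report response by age, sex and team.
4. Beside the unadjusted prevalence, give one standardised to the SIAP distribution in coarse age-sex groups. With 2 sexes and, for example, 4 age bands there are 8 groups, about 85 subjects each (683 / 8). Say that the register distribution includes people whom the study excludes.

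The cost is some extra invitations (a draw of about 893 to 1340 at the assumed 90% to 60% response), one weighting step with register data, and probably a slightly wider confidence interval for the standardised figure.

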#### Exclusion criteria

Alcohol intake > 30 g/day in males and > 20 g/day in females. Presence of chronic liver disease. Presence of the surface antigen of the hepatitis B virus or the presence of antibodies versus hepatitis C. Subjects with conditions or diseases hindering data collection and follow up of the study such as, incapacitating diseases, cognitive deterioration, institutionalized patients or subjects with no fixed address in any of the basic areas of the study. Subjects who do not provide written informed consent to participate in the study.

### Sample size

With an alpha risk of 0.05 for a precision of ± 0.03 percentage units in a bilateral contrast for an estimated proportion of 0.20 a randomized sample proportional to 683 subjects is required. Considering that 15% of the population will present alcohol intake or some previous liver disease, the number of patients to study in this percentage is increased making a total of 786 individuals necessary to fulfil the final sample size.

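### The 15% exclusion allowance is multiplied on instead of divided out, so 786 sampled subjects leave about 668 analysable rather than 683: a real but minor slip, immaterial to the prevalence estimate

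*Protocol article*

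**What the plan says.** The Sample size section sets out the inputs, the operation and the result.

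- Error rate and sidedness: "With an alpha risk of 0.05", "in a bilateral contrast".
- Target precision: "for a precision of ± 0.03 percentage units".
- Expected prevalence: "for an estimated proportion of 0.20".
- Resulting number: "a randomized sample proportional to 683 subjects is required".
- Allowance for exclusions: "Considering that 15% of the population will present alcohol intake or some previous liver disease".
- Inflated total: "the number of patients to study in this percentage is increased making a total of 786 individuals necessary to fulfil the final sample size".

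The abstract carries the inflated total as the study's sample: "A randomized sample of 786 subjects of 15 years or older were selected from the population".

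Three other sections bear on the reading. Exclusion criteria rules out alcohol intake above sex-specific limits and chronic liver disease. Selection method draws the sample at random from the population registered with the participating teams. Plan of analysis gives the prevalence with a 95% confidence interval.

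**The concern.** The number 683 is what must remain for analysis if the interval is to have the stated width. The 15% is described as a share of the population, and the sample is drawn from that population. The loss therefore applies to everyone sampled, not to the 683 who should be left. Adding 15% of 683 allows for too few exclusions, and the total said to fulfil the final sample size falls short of it. At stake is whether the one stated justification for the sample size agrees with itself, and whether the shortfall is large enough to affect the main prevalence estimate.

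**Working it through.** **Inputs.** All are from the Sample size section: two-sided alpha 0.05 (z = 1.96), p = 0.20, d = 0.03, required number 683, excluded share 15%, stated total 786. The source population of 360,000 is from Study subjects.

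**Step 1: reproduce 683.**
n = z² p(1 − p) / d² = 1.96² x 0.20 x 0.80 / 0.03² = 3.8416 x 0.16 / 0.0009 = 682.95, rounded up to 683. This is an exact match, so 683 is the number to be analysed.

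**Step 2: reproduce 786.**
683 x (1 + 0.15) = 785.45, rounded up to 786. This is an exact match, so the protocol multiplied.

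**Step 3: the operation that fits the stated assumption.**
If a share f of those sampled is excluded, N sampled leave N(1 − f). Setting N(1 − f) = 683 with f = 0.15 gives N = 683 / 0.85 = 803.5, rounded up to 804. The difference is 804 − 786 = 18 subjects (18 / 786 = 2.3%).

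**Step 4: could another convention give 786 by division?**
A finite-population correction with N = 360,000 gives a base of 681.6, so 682. Then 682 / 0.85 = 802.4 (803) and 682 x 1.15 = 784.3 (785). Neither is 786.

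**Step 5: what 786 delivers at 15% exclusions.**

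| Sampled | Analysable at 15% excluded | Half-width at p = 0.20 |
|---|---|---|
| 786 | 786 x 0.85 = 668.1 | 1.96 x √(0.16 / 668) = 0.0303 |
| 804 | 804 x 0.85 = 683.4 | 1.96 x √(0.16 / 683.4) = 0.0300 |

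The expected shortfall is 683 − 668 = 15 subjects. The Wilson interval also gives a half-width of 0.0303 at 668.

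**Step 6: break-even.**
786 leaves 683 only if exclusions are at most 1 − 683 / 786 = 13.1%. At a true 15%, the binomial probability of at least 683 analysable subjects is about 7% with 786 and about 54% with 804.

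**Step 7: the unit label.**
Read literally, 0.03 of a percentage point is d = 0.0003. That would need 3.8416 x 0.16 / 0.0003², about 6.8 million subjects, against a source population of 360,000. Only d = 0.03 as a proportion gives 683, so the intended meaning is clear.

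**The case against.** **The effect is negligible.** The precision is stated as 0.03, and 0.0303 rounds to it. This stands. A reader might infer that the study misses its precision target or that the design fails. The documents do not support that. The study is descriptive, and nothing in it sets a power threshold or decision rule for the prevalence estimate that 668 would fail and 683 would pass.

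**The inputs are less certain than the shortfall.** Both 0.20 and 15% are round planning values. With 668 analysable, a true prevalence of 19.4% already gives 1.96 x √(0.194 x 0.806 / 668) = 0.0300. At 13.8%, the figure that the Background cites for working males in Spain, the half-width is 1.96 x √(0.138 x 0.862 / 668) = 0.026. A prevalence above 20% would widen it. This also stands: the choice of p matters more than 0.03 of a percentage point.

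**The method is disclosed.** The text says that the number was increased by the percentage, so a reader can recompute it. That is true, but the total is then said to be what fulfils the final sample size, and under the stated assumption it does not.

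**Perhaps the 15% means 15 excluded per 100 eligible.** Multiplication would then be right, because 0.15 / 1.15 = 13.0% of those sampled would be lost and 786 would leave about 683. The text does not say this. It gives 15% of the population.

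**Perhaps 18 more subjects must be recruited.** A reader might infer this too, but it does not follow. The abstract describes the 786 as already selected, and the loss in precision does not call for further enrolment.

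**Conclusion.** The point holds as a minor arithmetic error. The stated total does not deliver its own target: about 668 analysable against 683, and a half-width of about 3.03 rather than 3.00 percentage points. It does not threaten the prevalence estimate.

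This rests on two assumptions. First, the 15% is a share of the people sampled, as the text says. Second, those people drop out of the analysis, as the Exclusion criteria imply. It also takes the 15% as the only loss. That figure names only alcohol intake and previous liver disease. The other exclusions, such as lack of consent or incapacitating disease, have no stated rate. If they are not covered elsewhere, the shortfall would be larger by an amount that the article does not allow one to calculate.

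The unit label is a slip of wording with no numerical consequence and adds no weight to the point.

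**What to change.** In Sample size, keep 786 and add that at 15% exclusions about 668 evaluable subjects are expected, for a 95% half-width of about ±3.03 percentage points at a prevalence of 20%. State alongside it that 804 (683 / 0.85) would be the total needed to retain 683. Remove the claim that 786 secures the final sample size.

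Editorial only: express the precision as ±3 percentage points, or as ±0.03 on the proportion scale.

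The cost is a sentence or two of text. Recruitment and analysis do not change.
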